### Secondary outcomes

4.2

The protocol may provide subsidy for implantation of metabolic rehabilitation programs in patients with other CVD such as dyslipidemia, hypertension among others.

### Data analysis

4.3

Data will be expressed as mean and standard deviation. The SPSS software version 24.0 will be used for statistics. The descriptive data will be measured by measures of central tendency and dispersion. The Shapiro–Wilk test will be used to verify the normality of the data. To compare the cardiorespiratory parameters, we will use the Friedmann test or the ANOVA test of repeated measures according to the normality of the data. The level of significance will be *P* < .05. All values will be compared with the rest condition.

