### Data collection

2.6

The evaluation instrument of the research will be applied before and after the practice of the proposed rehabilitation program. The instrument is based on the following collection protocol: BP, HR, Borg scale, respiratory rate, oxygen saturation, distance walked through the 6-minute walk test (6MWT), quality questionnaire (Which must be specific for each disease, and therefore the research used the diabetes quality of life-Brazil-DQOL), sleep quality questionnaire (Pittsburgh) and also the outcome variables that are glycated hemoglobin (sent by physician along with medical referral) and HRV through the cardiofrequency meter.

It is also suggested the insertion of cardiovascular and metabolic serum markers of individuals submitted to a metabolic rehabilitation program, in order to evaluate patients regarding cardiovascular risks.

With this evaluation, before and after the rehabilitation program, it will be possible to observe the response of these variables (Fig. 1).

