### Instruments

2.7

The main instrument is the HRV that will be evaluated in 2 ways: at rest and in exercise. At rest, to describe the autonomic profile of diabetic and exercise patients for 2 moments (pre- and postintervention) to observe the response to the stimuli offered to the patient during the stages (warm up—5 minutes, aerobic training—30 minutes, strength training—20 minutes, cool down—5 minutes) of metabolic rehabilitation.

In the first form of collection (at rest) patients will be placed in the supine position, where they will remain for 20 minutes in an air-conditioned room (22–25°), with a capture tape attached at the time of the xiphoid process. Such a brace has 2 electrodes attached to a sealed electronic transmitter, which pick up the heart's electrical impulses to which it is transmitted to the POLAR^[18]^ heart rate monitor attached to the volunteer's wrist.

In the second form of collection (in exercise), patients will undergo a metabolic rehabilitation program, however, previously they will also position the brace at the level of the xiphoid process to record the data and then initiate the intervention. This equipment will be positioned in the patient from the beginning of the metabolic rehabilitation and will remain until the end of the recovery.

The HRV will be analyzed by means of linear methods, analyzed in the domains of time and frequency, and also by nonlinear methods and the Poincaré plot.^[19]^

The analysis of the HRV will be performed from the heart beat recorded to beat throughout the protocol, and only series with more than 95% of sinus beats will be used for analysis.^[20]^

After the error check, the trace will be selected for analysis and subjected to a digital filtering, performed in Polar Precision Performance SW software (version 4.01.029). Finally, the HRV analysis will be done using the software: Kubios.^[15]^

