### Primary outcomes

4.1

Recruitment began in September 2016, and is underway. A total of 9 patients were evaluated and submitted to the intervention protocol by the end of June 2017.

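### For cardiorespiratory measures with one value before and one after the programme, the only named non-normal test (Friedman) is the sign test and ignores the size of each change

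*Protocol article*

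**What the plan says.** Section 4.3 (Data analysis) has one sentence on tests. It opens "To compare the cardiorespiratory parameters" and continues "we will use the Friedmann test or the ANOVA test of repeated measures according to the normality of the data". The choice between the two is made as follows: "The Shapiro–Wilk test will be used to verify the normality of the data". The threshold is given as "The level of significance will be *P* < .05", and the section ends "All values will be compared with the rest condition". It names no other rank test.

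Section 2.6 (Data collection) sets the timing: "The evaluation instrument of the research will be applied before and after the practice of the proposed rehabilitation program". The instrument covers blood pressure, heart rate, Borg scale, respiratory rate, oxygen saturation, 6-minute walk distance and heart rate variability (HRV), together with the two questionnaires and glycated haemoglobin.

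Section 2.7 (Instruments) records HRV both at rest and during exercise. It refers to "2 moments (pre- and postintervention" and lists four session stages: warm-up, aerobic, strength and cool-down.

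The only patient count is in section 4.1: "A total of 9 patients were evaluated and submitted to the intervention protocol by the end of June 2017". The article states no target sample size, effect size or power.

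**The concern.** The Friedman test is built for several conditions. It suits rest plus four stages. The same sentence is, however, the only stated non-normal route for every cardiorespiratory parameter, and some of these yield just two numbers per patient. Walked distance has no rest value and no stages. Resting HRV is a single recording at each evaluation.

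For such a pair, Friedman ranks each patient's two values 1 and 2 and keeps only which was higher. A gain of 5 m and a gain of 100 m in walked distance count the same. These are continuous measures, and the article gives no reason for reducing them to a direction. What is at stake is efficiency: a real change before to after is usually easier to miss than with a paired test that uses the size of the change.

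**Working it through.** **Inputs from the article.** Tests: Friedman or repeated-measures ANOVA (4.3). Occasions for the evaluation instrument: k = 2 (2.6). Alpha: 0.05 (4.3). Patients treated by the end of June 2017: 9 (4.1).

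**Assumptions, because the article gives no figure.** Two-sided testing; no ties; a further sample size of n = 20; within-patient changes (or log changes) normal with a standardised mean change of 0.6. The article has no power figure to reproduce.

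**Step 1: what Friedman becomes with two conditions.** The statistic is

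Q = 12/[n k (k+1)] × (sum of squared rank totals) − 3n(k+1).

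Let S of n patients rise. The rank totals are n + S (after) and 2n − S (before). With k = 2:

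Q = (2/n)[(n+S)² + (2n−S)²] − 9n = (2S − n)²/n.

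This is the sign-test chi-square. Check at n = 9, S = 8: the totals are 17 and 10, so Q = (2/9)(289 + 100) − 81 = 5.444, and (16 − 9)²/9 = 5.444.

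**Step 2: what it takes to reach significance.**

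| n | S | Q | p (chi-square, 1 df) |
|---|---|---|---|
| 9 | 7 | 2.78 | 0.096 |
| 9 | 8 | 5.44 | 0.020 |
| 20 | 14 | 3.20 | 0.074 |
| 20 | 15 | 5.00 | 0.025 |

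At n = 9, at least 8 of 9 patients must move the same way, however large the changes. The true size there is 2 × (9 + 1)/512 = 0.039, so the test does not exceed its nominal level.

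**Step 3: power of Friedman.** The chance that a patient rises is Φ(0.6) = 0.7257.

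- n = 9: 9 × 0.7257⁸ × 0.2743 + 0.7257⁹ = 0.190 + 0.056 = 0.246. The opposite tail is negligible.
- n = 20: P(S ≥ 15) for a binomial (20, 0.7257) = 0.518.

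**Step 4: power of the alternatives under the same assumptions.**

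- Paired t, from the non-central t distribution. At n = 9 the non-centrality is 0.6 × √9 = 1.80 with critical value 2.306, giving 0.354. At n = 20 it is 0.6 × √20 = 2.68 with critical value 2.093, giving 0.721.
- Exact Wilcoxon signed-rank, by simulation: about 0.30 at n = 9 and 0.70 at n = 20.

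| n | Friedman (k = 2) | Wilcoxon signed-rank | Paired t |
|---|---|---|---|
| 9 | 25% | 30% | 35% |
| 20 | 52% | 70% | 72% |

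**Step 5: how far this depends on the shape of the data (simulation).**

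- Lognormal before and after values, left untransformed: Wilcoxon gains 2 to 5 points at n = 9 and 8 to 15 at n = 20.
- Laplace (heavy-tailed) changes: the difference runs from about −1 to +4 points, for example 76% against 80% at n = 20.
- Changes with a long tail against the effect: the order can reverse. With exponential-type changes at n = 30 and a mean shift of 0.3 SD, Friedman has 71% and Wilcoxon 62%. The two tests no longer target the same quantity there, so this is not a pure power comparison.

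**The case against.** The strongest objection is that 4.3 may never have meant Friedman for a before-and-after pair. It says that values are compared with rest, section 2.7 supplies rest and four stages, and Friedman with repeated-measures ANOVA is the usual pairing for that layout. On this reading the article merely leaves the two-occasion test unnamed, which a condensed article may do.

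Much of this stands. Friedman is an ordinary choice for the stage data, and nothing here argues against it. But the sentence is written for the cardiorespiratory parameters as a whole. The registered title in section 5 uses that same term for outcomes after the programme, and walked distance cannot be compared with a rest condition at all. As written, the one stated fallback covers measures it does not suit.

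Several stronger readings are tempting, and the documents do not support them:

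- *That all listed measures have only two values.* Section 3 lists a pulse meter, oximeter, sphygmomanometer and symptom scale for the walk test, so heart rate, saturation, blood pressure and symptom score may be read more than once per evaluation.
- *That the point extends to glycated haemoglobin, quality of life or sleep.* Section 4.3 names no test for these.
- *That HRV will probably take the Friedman route because its indices are skewed.* The article says nothing about their distribution. It does not say whether normality is checked on raw values or on changes, and skewed raw values need not give skewed changes.
- *That a fixed amount of power is lost.* No such figure can be derived without an effect size and a target n.

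It is also fair that the sign test needs no symmetry of the changes, whereas Wilcoxon does.

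**Conclusion.** The point holds in a limited form. For walked distance and resting HRV, and for any other cardiorespiratory parameter with a single reading per evaluation, the stated non-normal route is the sign test. That it ignores the size of each change is exact and rests on no assumption beyond two values per patient.

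The cost in power is illustrative only. In the normal case of the table, Friedman falls short of Wilcoxon by 5 points at n = 9 and 18 at n = 20, and of the paired t-test by 10 and 20. Other shapes of change can remove or reverse the shortfall against Wilcoxon. A reader might infer that the results would be wrong. They would not: the test keeps its level, and validity is unaffected. This is an inexpensive improvement in efficiency.

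**What to change.** In section 4.3:

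1. Limit the Friedman test to comparisons of three or more conditions, such as rest and the session stages.
2. For cardiorespiratory measures with one value before and one after, judge normality on the within-patient changes and use a paired t-test, which equals a two-level repeated-measures ANOVA.
3. Where a positive measure is found to be right-skewed, run the paired t-test on the log scale and report the ratio of after to before with its 95% confidence interval.
4. Otherwise use the Wilcoxon signed-rank test with the Hodges-Lehmann estimate of the change.

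The cost is a few sentences. The methods are standard and no new data are needed. There are two small drawbacks: logged results are ratios rather than differences in the original units, and Wilcoxon assumes roughly symmetric changes. Where changes stay strongly skewed even after transformation, the sign test can remain as a sensitivity analysis.

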**Method::**

An experimental study of a randomized clinical trial type was therefore proposed to analyze the hemodynamic and glycemic response after the practice of a rehabilitation program in patients with type 2 diabetes mellitus (T2DM). In this clinical trial the patients will initially be submitted to an evaluation protocol that consists of assessing blood pressure, heart rate, Borg scale, respiratory rate, oxygen saturation, distance traveled through the 6-minute walk test, quality of life questionnaire, Pittsburgh sleep quality questionnaire, and still glycated hemoglobin and heart rate variability through the cardiofrequency meter. After careful evaluation of the patients, they will be submitted to a metabolic rehabilitation program composed of aerobic and resisted exercises, performed for 12 weeks, in 3 weekly meetings of 60 minutes each. With such evaluations, it will be possible to construct with evidence that it is possible to work safer metabolic rehabilitation programs in patients with T2DM or other diseases that generate cardiovascular risks, guaranteeing them an improvement in cardiorespiratory fitness, hemodynamic and glycemic variables, allowing improvement of the quality of life.

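### Section 4.3 fixes rest as the reference for all values and states no before-versus-after contrast, although the response to the 12-week programme is the trial's question

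*Protocol article*

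**What the plan says.** The abstract (Method) gives the aim as "to analyze the hemodynamic and glycemic response after the practice of a rehabilitation program". Section 2.6 (Data collection) sets the timing: "The evaluation instrument of the research will be applied before and after the practice of the proposed rehabilitation program". It also gives the reason: "With this evaluation, before and after the rehabilitation program, it will be possible to observe the response of these variables". The same section lists blood pressure, heart rate, 6MWT distance, DQOL, PSQI and others, and singles out glycated hemoglobin and HRV as the outcome variables.

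Section 2.7 (Instruments) defines a rest recording for HRV: 20 minutes supine, set against recording during warm-up, aerobic training, strength training and cool-down, with pre- and post-intervention moments.

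Section 4.3 (Data analysis) then says "To compare the cardiorespiratory parameters, we will use the Friedmann test or the ANOVA test of repeated measures", the choice depending on normality, and ends with "All values will be compared with the rest condition". The only other test named is Shapiro–Wilk, which is a normality check.

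**The concern.** The contrast fixed in section 4.3 does not match the question in the abstract and section 2.6. The question is what changes over 12 weeks. The stated reference is rest, and section 2.7 sets up rest as a recording condition only for HRV, as the counterpart of the exercise stages.

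An analyst who follows section 4.3 literally would report that HRV differs between exercise and supine rest. That would be expected whether or not the programme works. The change in resting HRV would have no stated comparison, and the reference rule has nothing to attach to for glycated hemoglobin, although it is one of the two named outcome variables.

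This goes beyond detail that a condensed article leaves to an analysis plan. The article states a contrast, and a later plan that follows it would inherit the mismatch.

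**Working it through.** The documents give no effect size, SD or power for this comparison, so there is no stated figure to reproduce. The check has three parts.

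**1. Which variables have a rest condition.**

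| Variable | Collected | Rest condition to serve as reference? |
|---|---|---|
| HRV | pre and post; rest and 4 stages | yes |
| Glycated hemoglobin | pre and post | no, one laboratory value per occasion |
| 6MWT distance | pre and post | no |
| DQOL, PSQI | pre and post | no, questionnaire scores |

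**2. What a within-session contrast with rest estimates.** Write the HRV value of patient i at moment m (pre, post) and condition s (rest, warm-up, aerobic, strength, cool-down) as

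Y(i,m,s) = a(i) + c(s) + d·[m = post] + e(i,m,s), with c(rest) = 0,

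where c(s) is the acute effect of the stage and d a programme effect common to all conditions. Within the post-programme session,

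Y(i,post,s) − Y(i,post,rest) = c(s) + e(i,post,s) − e(i,post,rest).

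The term d cancels exactly. If the programme effect differs by stage, the contrast becomes c(s) + d(s) − d(rest). That still mixes programme and acute effects unless it is compared with the pre-programme session, and section 4.3 states no such comparison. By contrast,

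Y(i,post,rest) − Y(i,pre,rest) = d + e(i,post,rest) − e(i,pre,rest),

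which responds to d directly.

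The HRV layout has 2 moments × 5 conditions = 10 cells per patient, in two crossed factors. Friedman handles one within-patient factor, so it cannot separate moment from stage or assess their interaction. Repeated-measures ANOVA can, if both factors are entered.

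**3. Illustration.** Assumed, not from the documents: between-patient SD 1.0, residual SD 0.7, stage effects 0, −0.5, −1.2, −1.0 and −0.4 (rest first), and d added to every post-programme value. There were 9 patients and 2000 runs per setting. Nine is the number treated by the end of June 2017 (section 4.1), not a planned size. Rejection rates at 0.05:

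| d | Post session, aerobic vs rest (paired) | Post session, Friedman over 5 conditions | Resting value, post vs pre (paired) |
|---|---|---|---|
| 0 | 0.875 | 0.771 | 0.048 |
| 0.5 | 0.893 | 0.780 | 0.274 |
| 1.0 | 0.889 | 0.774 | 0.778 |
| 1.5 | 0.904 | 0.793 | 0.981 |

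Variation down the second and third columns is simulation noise, since d cancels. With larger assumed stage effects (−0.5, −1.5, −1.2, −0.4; within-patient SD 0.35, between-patient SD 0.5), Friedman rejected in 100% of runs for d = 0, 0.3 and 0.6, while the paired pre/post test rejected in 4.5%, 36% and 88%. The level of the rest-referenced rate depends on what is assumed. Its failure to respond to d does not.

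The named tests can be run on two time points. Friedman then amounts to a sign test. With 9 patients, the exact two-sided P for 8 of 9 changes in one direction is 2 × (9 + 1)/512 = 0.039, and for 7 of 9 it is 2 × (36 + 9 + 1)/512 = 0.18.

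**The case against.** Several points on the other side are fair.

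- **Scope of the sentence.** It closes a paragraph whose only named comparison concerns cardiorespiratory parameters, so it may not be meant for laboratory values and questionnaires. The test for each further outcome could be left to an analysis plan. This stands in part: the absence of a named test for glycated hemoglobin is not, by itself, the point. What remains is that the wording covers all values and that the one contrast given is not the one section 2.6 calls for.
- **Meaning of rest.** A reader might infer that the plan never compares before with after. The text does not support that. If rest means the pre-programme rest recording, post-programme against pre-programme resting HRV would be one of the comparisons. The article does not say which rest is meant, so the supportable statement is that no pre/post contrast is stated. Even on that reading, glycated hemoglobin, 6MWT distance, DQOL and PSQI have no rest value to be compared with.
- **Applicability of the tests.** A reader might infer that the tests cannot be used on glycated hemoglobin or the questionnaires. They can; only the rest reference fails there. Likewise, the one-factor limit applies to Friedman and not to the repeated-measures ANOVA named beside it.
- **Purpose of the rest contrast.** Section 2.7 states an interest in the response to the stages of a session, and comparison with rest is a reasonable analysis of that aim. This stands.
- **The simulation.** Its flat rates follow from adding a uniform shift, and its inputs are assumed. This also stands: the algebra carries the argument, and the rates say nothing about this trial's power.
- **The remedy.** An uncontrolled pre/post change can also arise without a programme effect, for example through regression to the mean. The study is called randomized in the abstract and section 2, but the article describes no comparator. A paired test alone would therefore not supply a randomised comparison.

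**Conclusion.** The concern holds in a limited form. Section 4.3 fixes rest as the reference and states no before-versus-after contrast, while the abstract and section 2.6 make the response to the programme the question. Taken as a within-session comparison, the rest-referenced contrast loses a uniform programme effect completely, whatever the SDs or sample size. Four listed measures, including one of the two named outcome variables, have no rest condition. Friedman cannot carry the moment-by-stage structure of HRV; the repeated-measures ANOVA could.

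The exact cancellation assumes the same programme effect in every condition. With stage-dependent effects, the contrast is confounded with the acute response. The rejection rates are illustrative only. The documents do not show that a pre/post analysis is ruled out or that the named tests are unusable; they show that the contrast written down is the wrong one for the stated aim.

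**What to change.** Replace the last sentence of section 4.3 with three statements.

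1. **Glycated hemoglobin, resting HRV, 6MWT distance, blood pressure, DQOL and PSQI.** The target is the post-minus-pre change with a 95% CI and a paired test. If there is a randomised comparator, the target is instead the between-group difference in change, adjusted for the baseline value. If there is none, state that the result is an uncontrolled before/after change.
2. **Exercise HRV.** Use a two-factor repeated-measures ANOVA or a mixed model with time (pre/post), stage and time × stage.
3. **Comparison with rest.** Confine it to the within-session stage response described in section 2.7, and say which rest recording is the reference.

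The cost is a change of wording. Statements 1 and 2 use data already planned and need no new measurements. The sponsor has to state whether a comparator exists, because that decides which target applies in statement 1.

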## Ethics and dissemination

5

The study protocol was submitted and approved by the Research Ethics Committee of the Hospital das Clínicas do Acre through Opinion No. 1,616,721. Only participants who agree to provide written informed consent will be entered into the survey.

This registry of clinical trials was titled “Cardiorespiratory Parameters and Glycated Hemoglobin of Patients With Type 2 Diabetes After a Rehabilitation Program,” on March 28, 2017 in “ClinicalTrials.Gov” (NCT03094767).

## Discussion

6

The presence of cardiovascular risk factors as well as the presence of CVD contribute to an increase in the number of deaths, hospitalizations, and disabilities in the adult population. In view of this, primary care assistance with health promotion can be considered as the response to the modification of modifiable factors that influence the installation of risks and CVD, improving living conditions and creating favorable environments for health.^[27]^

The health promotion strategy represents an assertive alternative for addressing these risk factors.^[1]^ However, the multidisciplinary and transdisciplinary approach strengthens the actions in health, since the collaborative posture reinforces the purposes of prevention, control, and treatment of diseases. However, the inclusion of a protocol that includes a detailed evaluation followed by the implementation of metabolic rehabilitation will contribute to the construction of patient-centered care and its needs in order to improve people's health conditions.^[4,28]^
